## Abstract

**Background:**

Intramuscular pethidine is routinely used throughout the UK for labour analgesia. Studies have suggested that pethidine provides little pain relief in labour and has a number of side effects affecting mother and neonate. It can cause nausea, vomiting and dysphoria in mothers and can cause reduced fetal heart rate variability and accelerations. Neonatal effects include respiratory depression and impaired feeding. There are few large studies comparing the relative side effects and efficacy of different opioids in labour. A small trial comparing intramuscular pethidine with diamorphine, showed diamorphine to have some benefits over pethidine when used for labour analgesia but the study did not investigate the adverse effects of either opioid.

**Methods:**

The Intramuscular Diamorphine versus Intramuscular Pethidine (IDvIP) trial is a randomised double-blind two centre controlled trial comparing intramuscular diamorphine and pethidine regarding their analgesic efficacy in labour and their side effects in mother, fetus and neonate. Information about the trial will be provided to women in the antenatal period or in early labour. Consent and recruitment to the trial will be obtained when the mother requests opioid analgesia. The sample size requirement is 406 women with data on primary outcomes. The maternal primary outcomes are pain relief during the first 3 hours after trial analgesia and specifically pain relief after 60 minutes. The neonatal primary outcomes are need for resuscitation and Apgar Score <7 at 1 minute. The secondary outcomes are an additional measure of pain relief, maternal sedation, nausea and vomiting, maternal oxygen saturation, satisfaction with analgesia, whether method of analgesia would be used again, use of Entonox, umbilical arterial and venous pH, fetal heart rate, meconium staining, time from delivery to first breath, Apgar scores at 5 mins, naloxone requirement, transfer to neonatal intensive care unit, neonatal haemoglobin oxygen saturation at 30, 60, 90, and 120 mins after delivery, and neonatal sedation and feeding behaviour during first 2 hours.

**Discussion:**

If the trial demonstrates that diamorphine provides better analgesia with fewer side effects in mother and neonate this could lead to a change in national practice and result in diamorphine becoming the preferred intramuscular opioid for analgesia in labour.

**Trial Registration:**

ISRCTN14898678

Eudra No: 2006-003250-18, REC Reference No: 06/Q1702/95, MHRA Authorisation No: 1443/0001/001-0001, NIHR UKCRN reference 6895, RfPB grant PB-PG-0407-13170_IR5

## Background

Labour is generally considered to be a painful experience and analgesia is regularly required. Intramuscular opioids are one form of analgesia regularly employed. Intramuscular pethidine is routinely used throughout the UK for labour analgesia and is the only opioid licensed for independent use by midwives. There are a number of concerns in the literature regarding the use of pethidine. Some studies have suggested that pethidine provides little or no pain relief in labour, its main effect being to cause sedation rather than analgesia [1,2]. Pethidine also has a number of side effects on both the mother and the neonate which make it a less than ideal choice for labour analgesia. It can cause nausea, vomiting and dysphoria in women receiving it during labour [3]. It also crosses the placenta and can cause reduced fetal heart rate variability and fewer heart rate accelerations [4]. Effects on the neonate include respiratory depression, impaired feeding and altered crying [5-7].

Despite the disadvantages of pethidine, there are few large studies comparing the relative side effects and effectiveness of different opioids in labour and systematic reviews comparing parenteral opioids in labour have suggested a need for well-designed and suitably-sized trials of pethidine versus other opioids [8,9]. A small trial comparing intramuscular pethidine with diamorphine, showed diamorphine to have some benefits over pethidine when used for labour analgesia but the trial did not study the potential adverse effects of either opioid [10]. A national survey published in 2008 relating to use of intramuscular opioids for analgesia in labour in consultant-led units in the UK revealed that diamorphine was used in 34% of maternity units and was the most commonly used opioid for analgesia in labour in Scotland [11]. Where it is used, anecdotally it is perceived to provide superior analgesia with fewer side effects than pethidine, but to date there is no published large randomised controlled trial to support this impression. We aim to undertake a two-centre double-blind randomised controlled trial comparing intramuscular diamorphine and pethidine in terms of their analgesic efficacy in labour and their side effects in mother, fetus and neonate.

## Methods/design

This two-centre double-blind randomised controlled trial comparing intramuscular diamorphine and pethidine will be conducted at Poole Hospital NHS Foundation Trust (PHFT), the Sponsor site, and the Royal United Hospital, Bath (RUH). Southampton and South West Hampshire Ethics Committee granted ethical approval. Information about the trial will be provided to women and consent obtained in the antenatal period via the antenatal clinics, both in the community and maternity hospital, or in early labour in the delivery suite prior to the request for analgesia. Consented women will be recruited to the trial when there is maternal request in labour for opioid analgesia.

### Inclusion criteria

The women recruited will be those who have given written informed consent, who are in active labour with a singleton pregnancy, defined as regular uterine contractions of at least 2 in 10 minutes and cervical dilatation of at least 3 cms, with fetal gestational age of 37-42 weeks and a minimum weight of 60 kg. Competent women of sixteen years old or older are eligible. Both multiparous and nulliparous women will be eligible including those who have either gone into labour spontaneously or who have had an amniotomy and intravenous oxytocin to induce labour.

### Exclusion criteria

Exclusion criteria include lack of informed consent, allergy or previous severe reaction to opioid analgesia, opioid dependency, use of parenteral opioids within the previous 24 hours, history of fetal compromise, maternal cardiorespiratory compromise, ASA 3 & 4 (severe systemic disease including threat to life), maternal weight greater than 120 kgs or less than 60 kg.

### Allocation of analgesia

Once recruited, women will be randomly allocated to receive either intramuscular pethidine 150 mg or diamorphine 7.5 mg into the gluteus muscle or muscles of the lateral thigh. Qualassept Ltd is supplying the pre-filled syringes of pethidine and diamorphine to the respective pharmacies in Poole Hospital NHS Foundation Trust or the Royal United Hospitals Bath NHS Trust. The study drug will be dispensed in batches of two syringes by pharmacy. The syringes will be labelled only with a trial number in order to conceal group allocation from both the midwife and the parturient, and to ensure that if two doses are given, the same opioid is given both times. Randomisation will use random block sizes between 2 and 10 to ensure approximately equal group sizes, be stratified by centre and generated using PEPI [12]. The method is administered by the pharmacies and ensures parturients, researchers, maternity unit staff and trial statistician are blind to allocation. Parturients will also receive Metoclopramide 10 mg with the first dose, in line with current department prescribing guidelines. A maximum of two doses of opioid may be given with a minimum interval of 2 hours if the women requests additional analgesia. Regional analgesia or Entonox will be available as rescue analgesia.

## Measurements

• *General demographics*. Age, weight, gestational age, cervical dilatation at first request for analgesia, frequency of contractions, parity, spontaneous or induced labour, use of syntocinon, presentation, mode of delivery, drug administration to delivery interval. This information will be derived from the maternal notes and interview with the midwife taking care of the parturient.

• *Maternal Pain Evaluation*. Pain severity during last contraction will be assessed using a visual analogue score (VAS) (with anchor points of 0 = no pain at all and 10 = the most excruciating pain) and verbal scales of pain intensity during the last contraction (pain intensity score: 0 = no pain; 1 = mild pain; 2 = moderate pain; 3 = severe pain). In addition, the midwife will assess pain relief during the previous 30 minutes (pain relief score: 0 = none; 1 = slight; 2 = moderate; 3 = good, 4 = complete).

• *Maternal Sedation and Vomiting Evaluation*. Maternal sedation during the previous 30 minutes will be assessed by the midwife using sedation scores (0 = alert; 1 = mild i.e. occasionally drowsy and easily aroused; 2 = moderate sedation i.e. frequently drowsy but still easily aroused; 3 = severe sedation i.e. somnolent and difficult to rouse) and by measuring maternal oxygen saturation by pulse oximetry. Maternal pulse oximetry measurement is integral within the cardiotocograph (CTG) machine (Phillips PN/2703A) at the RUH and using the Masimo Rad 5 machine at PHFT. Vomiting will be assessed as a side effect with a yes/no answer pre-dose and during each subsequent thirty minutes period.

Maternal assessments will be made when the woman first requests analgesia and then every thirty minutes after the trial drug has been given, for a maximum of three hours or until delivery has occurred or additional analgesia is requested. A further 3 hours of measurements are then made if additional opioid analgesia is requested not less than 2 hours after the first dose. The parturient's overall satisfaction with the analgesia will also be assessed 12-24 hours post partum as well as their wish to choose the same opioid for their next labour analgesia.

• *Fetal Monitoring*. Fetal well-being will be monitored by continuous monitoring of fetal heart rate baseline and variability according to standard department protocols and classified as **Reassuring **(baseline 110-160 bpm, variability >5 bpm, no decelerations and accelerations present); **Non-reassuring **(baseline 100-109 or 161-180, variability of <5 for >40 but <90 minutes, and early or variable decelerations or a single prolonged deceleration up to 3 minutes) or **Abnormal **(Baseline <100 or >180 or sinusoidal pattern for >10 minutes, variability of <5 for >90 minutes, and atypical variable decelerations or late decelerations or a single prolonged deceleration of greater than 3 minutes). CTG monitoring is made using Corometrics 170 series machine in PHFT and using the Phillips PN/2703A machine at RUH. If meconium staining occurs then the time of first appearance in relation to administration of trial drug will be noted. At delivery cord blood will be taken for measurement of umbilical arterial and venous pH.

• *Neonatal Monitoring*. Neonatal condition will be assessed by time to first breath, Apgar score at 1 minute and 5 minutes, need for naloxone, need for resuscitation by bag mask ventilation or intubation and transfer to Neonatal Intensive Care Unit (NICU). Neonatal oxygen saturation will also be measured every 30 minutes from birth for 2 hours using the Masimo Rad 5 pulse oximeter at PHFT and Mindray PM-60 at RUH. Neonatal sedation in the first 2 hours of life will also be recorded using the same scoring system as the parturient. Time from delivery to first feed will be recorded as well as a subjective assessment of feeding behaviour by the midwife (0 = normal; 1 = mildly depressed rooting and sucking behaviour; 2 = severely depressed rooting and sucking behaviour) during the first 2 hours of life.

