##### Pain relief at 60 minutes

Measured by change from baseline in pain intensity VAS at 60 minutes. The dose of analgesia is administered intra-muscularly, and it is anticipated that maximum analgesic effect will occur at around 60 minutes after administration. Pain intensity at 60 minutes was the primary outcome used by Fairlie et al [10], and is the basis of our sample size calculation.

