##### Other

(e) Maternal sedation score over first 3 hours

(f) Time from first dose to delivery

(g) Entonox or regional analgesia given

(h) Nausea over 3 hours

(i) Vomiting over 3 hours

(j) Oxygen saturation over 3 hours after each dose of study drug or until delivery

(j) Percent reporting that they would choose the same pain relief in their next pregnancy

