## Sample Size

The number of women to be recruited has been determined using a sample size calculation, and is based upon the maternal primary outcome measure of pain relief at 60 minutes, and the neonatal primary outcome measures of Apgar score < 7 at 1 minute and neonatal resuscitation. We could find no data on our specific maternal primary outcome on which to base the sample size calculation (i.e. change in pain intensity). However, Fairlie et al in their randomised trial of pethidine versus diamorphine [10] reported on VAS pain intensity at 60 mins post administration of the first dose, and we have based our sample size calculation upon this. A standard deviation (SD) for pain intensity post opiate administration can be estimated from the data they present (SD = 2.6), and we have estimated the SD of change in pain intensity using 3 scenarios of different correlations between post-analgesia and pre-analgesia scores; correlations of 0.3, 0.5 and 0.7 give SDs of 3.1, 2.6 and 2.0 respectively. A 1 cm difference on a 10 cm VAS represents 10% of the scale, and to detect mean differences of this magnitude between the two arms of the trial with 90% power (at the 5% significance level) will require sample sizes of 203, 144 and 86 per group respectively in the 3 scenarios. A 1 cm difference is similar to the difference in pain intensity at 60 minutes found by Fairlie (0.9), is not larger than the 1.4 cm identified by Holdgate et al [13] as being the minimum change in pain that can be subjectively identified by patients with acute pain, and represents a standardised effect size of 0.38. We will set sample size at the higher figure of 203 per group.

Regarding neonatal outcomes, the Fairlie trial found that around 30% of neonates required resuscitation, and that around 25% of neonates whose mothers were given pethidine had 1 minute Apgar scores of less than 7 [10]. Thus with 203 participants per group the study will have 90% power to detect reductions of around 50% in both these outcomes (i.e 30% v 16% and 25% v 12% respectively). The difference for Apgar scores is similar to that found by Fairlie et al [10].

Initially we will aim to recruit 450 to allow for the fact that not all women will have data on pain intensity, for example if they delivered soon after administration of the trial drug. However we will monitor this during the trial and alter our recruitment target accordingly.

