## Statistical Analysis

Women will be analysed in the group to which they were originally randomised, regardless of what subsequently occurred during their labour. To enable this, where appropriate, all measures will be collected on all women once they have been randomised. However, within this framework, women could still, at any time, withdraw their consent to be in the trial.

Data will be analysed using SPSS for Windows and MLWin [14]. Significance tests will use a 5% two-sided significance level. Randomisation will be stratified by study site, and this will be controlled for in all analyses. Given the design of the trial, it is anticipated that missing data will be mostly negligible. The exception will be for the observations taken at 30 minute intervals after administration of the trial drug, where observations will cease if the mother delivers. We will assume these missing data are "missing at random" [15]. Analysis of the two maternal primary outcome measures will be as follows. Pain relief will be measured at 30 minute intervals over 3 hours. The repeated measures nature of the data will be taken into account using a maximum likelihood based multi-level (mixed) model [14]. This model permits analysis of unbalanced repeated measures data thus avoiding exclusion of participants with incomplete data [14]. Initially the interaction between trial group and timing of pain VAS measurement will be tested to see if the effects of the study drug change over time. If the interaction effect is not statistically significant, the interaction will be removed from the multi-level model and the main effect of trial group tested. Parameter estimates with 95% confidence intervals will be presented. The second maternal primary outcome measure, mean difference in pain relief at 60 minutes, will be estimated using multiple regression.

The neonatal primary outcomes, need for resuscitation and Apgar score under 7 at 1 minute, will be compared between groups using logistic regression, and the results presented as odds ratios (95% CI) and Numbers Needed to Treat (NNT).

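### Scheduled maternal side-effect recording stops at delivery, so the three-hour poor-result proportions compare women with unequal follow-up

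*Protocol article*

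**What the plan says.** Under Measurements, maternal assessments are made at the first request for analgesia and again at 30-minute intervals after dosing. They continue "for a maximum of three hours or until delivery has occurred or additional analgesia is requested". The same section describes the pain scales, the midwife's sedation score, maternal pulse oximetry and a yes/no record of vomiting, and gives no separate stopping rule for any of them. A second opioid dose starts a further 3 hours of measurements.

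Statistical Analysis confirms the stop, describing 30-minute observations "where observations will cease if the mother delivers", and assumes that the resulting gaps are missing at random.

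The secondary outcome list (Maternal, Other) is not uniform. Sedation is "Maternal sedation score over first 3 hours", and nausea and vomiting are likewise over 3 hours, none with a delivery limit. Oxygen saturation, in the same list, runs for 3 hours after each dose or until delivery. Time from first dose to delivery is in that list too.

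Statistical Analysis then plans two analyses of these repeated categorical outcomes: (a) repeated-measures models, and (b) logistic regression on the proportion of women with a poor result at any point in the three-hour follow-up.

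**The concern.** A rule that ends at delivery suits pain, which is scored for the last contraction. It does not suit sedation, saturation, nausea or vomiting, which can still be measured after delivery and which the trial wants to attribute to the drug over a fixed window.

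The consequence falls mainly on analysis (b). An any-poor-result proportion assumes that every woman was watched for the same time. Here she is watched until she delivers, asks for more analgesia or reaches 3 hours. The first two occur after randomisation, and time to delivery is itself compared between arms. If one drug is followed by earlier delivery, its women have fewer readings and fewer chances to record a poor result, so that drug looks safer for a reason unrelated to side effects. The abstract and Discussion both make fewer side effects part of the case for changing national practice.

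**Working it through.** **1. Readings available after the first dose.** Inputs: 30-minute spacing, 3-hour maximum, stop at delivery (Measurements). Scheduled points are 30, 60, 90, 120, 150 and 180 minutes, so 180/30 = 6.

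| Delivery after first dose | Scheduled post-dose readings |
|---|---|
| under 30 min | 0 |
| 30-59 min | 1 |
| 60-89 min | 2 |
| 90-119 min | 3 |
| 120-149 min | 4 |
| 150-179 min | 5 |
| 180 min or later | 6 |

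These are maxima, since a request for additional analgesia can end recording sooner.

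**2. How many women are affected.** The article gives no figure. Sample Size recruits 450 to obtain 406 with data: (450 - 406)/450 = 44/450 = 9.8%. That allowance is for missing pain data for any reason; women are mentioned "if they delivered soon after administration of the trial drug" only as an example. It is not an estimate of the share delivering within 30 or 60 minutes.

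**3. Effect of fewer readings on analysis (b).** Assume a risk p of a poor result in each interval, independent between intervals and equal in both arms. The values of p are assumptions. The chance of any recorded poor result over k readings is 1 - (1 - p)^k.

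| p | k = 1 | k = 6 |
|---|---|---|
| 2% | 2.0% | 11.4% |
| 5% | 5.0% | 26.5% |
| 10% | 10.0% | 46.9% |

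**4. Effect on the comparison.** Let a share q of an arm have one reading and the rest six. The recorded proportion is q × p + (1 - q) × [1 - (1 - p)^6]. Assume q = 5% in one arm and 15% in the other. For p = 5%:

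- first arm: 0.05 × 0.05 + 0.95 × 0.265 = 0.254
- second arm: 0.15 × 0.05 + 0.85 × 0.265 = 0.233

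| p | q = 5% | q = 15% | Spurious difference |
|---|---|---|---|
| 2% | 10.9% | 10.0% | 0.9 points |
| 5% | 25.4% | 23.3% | 2.1 points |
| 10% | 45.0% | 41.3% | 3.7 points |

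The true risk is the same in both arms throughout. If q is also the same, the spurious difference is zero, although both proportions understate the three-hour risk.

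**5. Whether the missing-at-random assumption repairs this.** It can support analysis (a), which uses whatever intervals were observed. It does nothing for (b) if a woman with no poor result in one reading is entered as having none in three hours. The article does not say how such women are entered.

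**The case against.** A reader might infer that early deliverers have little or no maternal safety data. The article does not support that. Under Adverse Event Reporting, adverse events are documented for the duration of the study, with onset, interval from first dose, severity and causality, and serious events arising from the trial drugs are reported until 30 days after the last dose. Neither stops at delivery. But event reports do not supply the scheduled scores and saturations on which these secondary outcomes rest.

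A reader might also infer that recording stops before the drug's peak side effects. The article says "it is anticipated that maximum analgesic effect will occur at around 60 minutes after administration", which concerns analgesia; it gives no peak for sedation, desaturation or vomiting. The point needs only the protocol's own 3-hour window.

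Nor does delivery soon after a second dose mean no data. Doses are at least 2 hours apart, so such a woman may have up to four readings from the first dose (30, 60, 90 and 120 minutes), unless an earlier request for analgesia ended them.

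The strongest defence is that the stop is openly stated, that a trial of analgesia in labour may reasonably end its scheduled readings at delivery, and that the missing 3-hour qualifier is shorthand, since the pain outcomes are worded the same way. Much of this stands. Analysis (a) is a sensible response to incomplete series, and no primary outcome is touched. What remains is that the stop is not justified separately for side effects, that the outcome list qualifies saturation but not its neighbours, and that (b) is described as covering a follow-up that some women will not complete.

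**Conclusion.** The point holds for scheduled side-effect readings and for analysis (b). Women who deliver within an hour of the first dose contribute none or one of six readings, and the outcome windows for sedation, nausea and vomiting do not match the measurement rule. Comparisons under (b) are biased if the drugs differ in time to delivery, in favour of the drug with the shorter time. The article does not show that they differ, so bias is conditional, not established.

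The size is likely to be modest: 0.9 to 3.7 percentage points in the illustration. That rests on assumed interval risks of 2% to 10%, independence between intervals, and an assumed 5% v 15% split in women with one reading, none of which is in the article. The sample size of 203 per group is unaffected. The change is worth making because it is cheap and because maternal side effects are part of the trial's stated question.

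**What to change.** These changes concern data collection and analysis only, not care.

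1. **Separate the stopping rules in Measurements.** Keep the contraction-based pain measures ending at delivery. Record sedation, nausea and vomiting at each 30-minute point to 3 hours after the most recent dose, regardless of delivery or a request for further analgesia, and flag readings taken after delivery. Extend maternal saturation in the same way only where an oximeter is available.
2. **Reconcile the windows** in Measurements, the secondary outcome list and Statistical Analysis, so that each outcome has one stated window.
3. **Correct analysis (b).** Where readings remain truncated, do not count unobserved intervals as event-free. Either base inference on the repeated-measures model in (a), with the crude proportions as description, or account for the observed time at risk.

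**Cost.** A protocol and case report form amendment, and a few extra midwife readings after delivery. Sedation and vomiting need no equipment, and staff are already with the baby: "Neonatal oxygen saturation will also be measured every 30 minutes from birth for 2 hours". Saturation is harder: at the Bath site maternal oximetry is built into the cardiotocograph, so a separate oximeter may be needed, and at Poole the same oximeter model is named for mother and baby. If only one site can extend it, the arms remain comparable within site, because randomisation is stratified by centre and analyses control for it. Some post-delivery readings will reflect delivery-related events as well as the drug, hence the flag.

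### Pain scoring stops when a woman requests additional analgesia, but the analysis section names only delivery as the reason scores end and bases its missing-at-random assumption on that

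*Protocol article*

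**What the plan says.** Under Measurements, maternal assessments are made at the first request for analgesia and then every 30 minutes after the trial drug, "for a maximum of three hours or until delivery has occurred or additional analgesia is requested". The next sentence provides one restart: "A further 3 hours of measurements are then made if additional opioid analgesia is requested not less than 2 hours after the first dose". Under Allocation of analgesia, "Regional analgesia or Entonox will be available as rescue analgesia". No restart is described for either of these.

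The Statistical Analysis section states: "Given the design of the trial, it is anticipated that missing data will be mostly negligible". Its one exception is the 30-minute series, "where observations will cease if the mother delivers", and it assumes that those gaps are missing at random. It also states: "Women will be analysed in the group to which they were originally randomised, regardless of what subsequently occurred during their labour". To that end, and where appropriate, "all measures will be collected on all women once they have been randomised".

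The first maternal primary outcome is change in pain intensity over 3 hours, analysed with a likelihood-based multi-level model. The second is change in VAS at 60 minutes, analysed with multiple regression. Adjustment for pre-administration pain is listed as supplementary.

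**The concern.** Data collection has two early stopping events and the analysis section knows of one. The omitted event is the one tied to the outcome: a woman asks for more analgesia largely because of the pain she has at that moment. No VAS is specified at the request, and the later scheduled scores are not taken. If one drug relieves pain less well, more women in that arm leave the series, and they tend to be those in most pain.

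Missing at random may be reasonable for delivery. For a request it needs its own justification, and the document gives none. Both maternal primary outcomes use these scores. An analysis plan written later can choose a model, but it cannot recover scores that were never recorded.

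**Working it through.** **1. The two sections side by side.**

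| | Measurements | Statistical Analysis |
|---|---|---|
| Series ends at 3 hours | yes | yes |
| Series ends at delivery | yes | yes |
| Series ends at request for additional analgesia | yes | not mentioned |
| Series restarts | second opioid requested at 2 hours or later | not mentioned |

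The Sample Size section also gives only early delivery as its example of missing pain data. The secondary outcome of maternal oxygen saturation runs until delivery, with no stop at a request. The restart sentence specifies opioid analgesia while the stopping sentence does not, so the stop naturally covers regional analgesia and Entonox too.

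**2. Who is affected.** Women who request regional analgesia or Entonox at any time within 3 hours, or any additional analgesia before 2 hours, have no restart. A woman who requests a second opioid between 2 and 3 hours starts a new series inside the first 3-hour window. The text does not say whether those scores count toward the 3-hour outcome.

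**3. The plan's own sample size.** SD of change = 2.6 × √(2(1 − r)), which is 3.08, 2.60 and 2.01 for r = 0.3, 0.5 and 0.7. For 1 cm, SD 3.1, 90% power and two-sided 5%: n = 2 × 3.1² × (1.960 + 1.282)² ≈ 202 per group, or 203 with the t distribution. The stated 203 reproduces. Recruiting 450 for 406 with data allows 1 − 406/450 = 9.8% loss.

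**4. Three-hour outcome (illustrative).** The document gives no request rates, so all rates below are assumed. The true difference is 1.0 cm and the VAS SD is 2.6.

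- *Simulation A:* 100,000 women, random intercept with 40% of the variance, AR(1) residual with correlation 0.5, unstructured normal likelihood fit. With 36–44% (worse arm) and 24–29% (better arm) stopped by 180 minutes, the estimate is 0.83 or 0.92 cm when requests follow current unrecorded pain. It is 0.94 cm when they follow current and previous pain equally, and 1.01 cm when they follow recorded pain only.
- *Simulation B:* 6,000 women, equal correlation of 0.5, random-intercept model adjusted for baseline. Requests on current pain give 0.79 cm (61% v 45% stopped by 180 minutes) and 0.85 cm (45% v 30%). Requests on recorded pain give 1.03 and 0.97 cm (standard error 0.04), consistent with no bias.

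**5. Sixty-minute outcome (Simulation B settings, 400,000 women).**

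| Requests follow | Lost at 60 min, worse arm | Lost, better arm | Change score | Baseline-adjusted |
|---|---|---|---|---|
| current unrecorded pain | 8–35% | 4–23% | 0.89–0.97 cm | 0.76–0.91 cm |
| recorded pain only | 4–21% | 2–13% | 0.99–1.00 cm | 0.93–0.97 cm |

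The unadjusted change score is closest to the stated main analysis. Its lack of bias in the last row follows from the assumed correlations: Cov(60-min − baseline, 30-min) = σ²[ρ(30,60) − ρ(0,30)], which is zero when the two correlations are equal. If scores after the drug correlate more strongly with each other than with baseline, it is not zero and attenuation returns.

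**6. Power for the 3-hour outcome.** Under Simulation A's covariance, the variance of (mean of six scores − baseline) is 0.6 × 2.6² × [14.0625/36 + 1 − (2/6) × 0.984] = 4.056 × 1.0625 = 4.31, so the SD is 2.08. With 203 per group, SE = 2.08 × √(2/203) = 0.206. Power = Φ(estimate/SE − 1.96), which is 99.5%, 99.4% and 98.1% for 0.94, 0.92 and 0.83 cm. With a further assumed 30% loss of information it is about 97%, 96% and 92%.

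**The case against.** Several points on the other side are sound.

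- The analysis section does not say that delivery is the *only* reason for stopping, and its commitment to collect all measures applies where appropriate. A reader might infer that the plan breaks a flat promise of complete data. With that qualifier, it does not. What stands is that the one exception to negligible missingness is described by delivery alone.
- Recording does restart for a second opioid at 2 hours or later, so the gap is narrower than every request.
- The mixed model uses every recorded score. If those scores explain the requests, missing at random can hold for the 3-hour outcome. A reader might infer that both maternal primary outcomes *are* biased; the documents support only that they *can* be.
- A reader might set 0.83 to 0.94 cm against the planning SD of 3.1 and infer power of 77% to 86%. That SD is for change at a single time point under the most pessimistic correlation. It does not apply to a six-score mean, and step 6 shows no drop below 90%.
- If the drugs act alike on pain and on requests, the stopping rule creates no false difference.
- The Sample Size section promises to monitor completeness and adjust recruitment. That restores numbers but does not remove selective loss.
- Scores after rescue carry a cost too. Assuming 36–37% v 26–28% stopped and rescue lowering VAS by 2–4 cm, analysing all scores turned 1.0 cm into 0.80–0.92 cm. Continuing to score therefore fits the as-randomised rule but is no cure for attenuation.
- A sensitivity analysis may already exist in an analysis plan that is not shown, so its absence is not itself the fault.

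**Conclusion.** The inconsistency is real and lies in the text: the stopping rule used at the bedside includes a pain-related event that the analysis section does not recognise when it justifies missing at random. The handling of scores after a second dose is also left open.

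The consequence is conditional. If requests are driven by pain not yet recorded, a true 1.0 cm over 3 hours is estimated at roughly 0.8 to 0.9 cm. If recorded scores explain the requests, the 3-hour model is about unbiased, and a 60-minute regression without the 30-minute score ranges from unbiased to slightly attenuated. These sizes rest on assumed request rates, correlations and normally distributed scores, so they show direction and order of magnitude only. No shortfall in power for the 3-hour outcome is established.

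This should be fixed, and before recruitment, but it does not invalidate the design.

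**What to change.** - **Measurements:** continue the 30-minute VAS to 3 hours or delivery whether or not additional analgesia is requested. Take a VAS at the request, and record the time and type of any additional analgesia. This concerns scoring only and changes no treatment.
- **Statistical Analysis:** name requests for additional analgesia as a cause of missing scores if any remain. State that scores after a request or a second dose within the first 3 hours are analysed under the existing as-randomised rule.
- **Sensitivity analysis:** add, here or in the analysis plan, one analysis that drops post-request scores and replaces missing at random with an unfavourable shift, for example 1 and 2 cm. Report it beside the main result.

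The cost is a few extra VAS entries per woman by staff already present, a wording amendment and one further analysis. The drawback is that post-rescue scores partly reflect the rescue and can also shrink the difference, which is why both analyses should be reported.
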